# Measuring Behavioural Change during Covid-19 Epidemic

## Introduction and Rationale

Appropriate response to Covid-19 requires an understanding of the epidemiological and behavioural drivers of disease transmission. Due to the dynamic nature of the epidemic and with the spread of the disease in the UK and Europe, analyses of the main factors affecting transmission need constant updating to provide relevant data-driven evidence to inform public health policies.

The predictive capabilities of mathematical models have been transformed through quantifying social contact rates. However, these data (such as the POLYMOD survey) were collected in “peace-time” and individuals’ behaviour may change during a severe epidemic.

Social mixing, a key determinant of COVID-19 spread, is likely to change over the course of the epidemic in relation to health risk perception. Therefore, timely data on social contacts and uptake of protective behaviours will be needed for shaping public health messaging and monitoring its effectiveness. These data will also be essential for improving transmission models and forecasting.

We will conduct a contact survey to assess changes in social mixing in relation with health risk perception. We will monitor contact patterns in the United Kingdom, Belgium and the Netherlands populations over the course of the epidemic, and assess psychological factors associated with contact. Behaviour tracking will be integrated in real-time models to improve the efficacy of public health interventions (e.g. messaging) and epidemic forecasts. These data will be used to refine transmission models, improve forecasting, and assess the effectiveness of social distancing measures.

We will simultaneously ask participants about knowledge, uptake and perceived efficacy of certain interventions (such as home-working). We will ask about cases in their social networks and the country, and measure how their behaviours change if/when they become unwell. Linking (at an individual-basis) changes in perceived and actual risk and changes in perceived efficacy of interventions with the uptake of different precautionary behaviours and individuals actual contact patterns will give unparalleled quantitative insight into how and why behaviours change during an epidemic.

Individuals will be regularly surveyed (every 2 weeks) to track if behaviours alter and what influences this. To our knowledge, this is the first time such data will be collected over the

course of an epidemic. The development, piloting and analysis of the work will be led by [name] (University of Antwerp) and [name] (London School of Hygiene and Tropical Medicine). Real-time analysis and presentation of the data will be conducted by the LSHTM team, with additional input from partner organisations (RIVM, Bern, ISI Turin).

## Aim and objectives

This study aims to identify the impact of social distancing interventions implemented by the government and the perceived and actual threat of the Covid-19 epidemic on social mixing behaviours.

We will do so using the following objectives.

1. To collect accurate estimates of the following data during the Covid-19 outbreak
  - a. Frequency of age-specific social contacts and their characteristics, at different points in the epidemic
  - b. Household and individual level exposures to social distancing interventions
  - c. Uptake of individual preventive measures
  - d. Changes in attitudes and risk perceptions regarding the Covid-19 epidemic
2. To create social contact matrices that can be used to parametrize epidemiological transmission models
3. To assess the impact of different social distancing interventions on social mixing within the population
4. To use mathematical models to inform public health policy decisions related to Covid-19 outbreak.

## Study design

We will follow a cohort of adults prospectively during the course of the Covid-19 epidemic in the United Kingdom, Belgium and the Netherlands. We will ask questions about social contact behaviour, personal preventive measures, and exposure and impact of different social distancing interventions that may be implemented.

### **Enrolment procedure**

We aim to survey 500 adults per country every two weeks using an online survey, for a total of ten weeks (five surveys). The study will be conducted among individuals who are already subscribed to internet panels from a market research company, in the United Kingdom, Belgium

and the Netherlands. The company will ensure a sample that is representative of the national population on age of adults, sex, geographical location, and socio-economic status.

Panel members will be invited to participate by email on a random day of each week of data collection. In case of non-response, we will send up to two reminder emails for every week. Members who indicate that they no longer want to participate in this survey, will be replaced with other members of the internet panel with similar age and sex.

Participants will be paid an incentive for every survey they complete to compensate for their time..

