## Statistics and data analysis

### Sample size

We will measure social contact rates every 2 weeks in a panel of 500 individuals using diary-based methods. The precision around the average number of daily contacts in any age group will depend on the actual average number of daily contacts and degree of overdispersion in the distribution of the number of contacts. We estimate that with two records per individual we can detect a difference of 2.5 contacts between pairs of observations with 90% power, 5% Type 1 error, and 20% loss to follow up. Therefore repeated measurement of individuals should provide adequate power for further assessment of other endpoints.

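### Replacements are matched on age and sex only, so the stated representativeness on region and socio-economic status is not preserved and wave composition may drift

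*Protocol*

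**What the plan says.** All the sampling rules are in the protocol's Enrolment procedure section.

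- **Size and schedule:** "We aim to survey 500 adults per country every two weeks using an online survey, for a total of ten weeks (five surveys").
- **Standard for the sample:** the panel company is to deliver one that is "representative of the national population on age of adults, sex, geographical location, and socio-economic status".
- **Who is replaced, and by whom:** "Members who indicate that they no longer want to participate in this survey" are the only people the rule covers. They "will be replaced with other members of the internet panel with similar age and sex".
- **Silent non-response:** "In case of non-response, we will send up to two reminder emails for every week". No replacement is stated if the reminders fail.

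Other sections bear on the point. Study design says "We will follow a cohort of adults prospectively during the course of the Covid-19 epidemic". Sample size claims the ability to "detect a difference of 2.5 contacts between pairs of observations with 90% power, 5% Type 1 error, and 20% loss to follow up", on the basis of two records per person. Statistical analysis plans multilevel count models, with age, sex and household size named and the list of confounders left open. It corrects the contact matrices for the population's age structure, and no other population margin is mentioned there. The Survey section collects employment status and income at each respondent's first survey.

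**The concern.** The sample is balanced on four variables at recruitment, but the maintenance rule names two. A withdrawing member may be replaced by someone of the same age and sex from another region or socio-economic group. A member who goes silent leaves a gap that the rule does not fill. If loss differs by region or socio-economic status, the realised sample can move away from the population on exactly the two variables that the replacement rule omits.

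This matters because the objectives ask for contact frequencies at different points in the epidemic and for matrices to feed transmission models. The Dissemination section promises findings within days of each wave, to inform decisions on scaling interventions up or down. Socio-economic status and region are plausibly related to contacts, for example through the chance of working from home, which the survey itself measures. A change in who answers could then be read as a change in behaviour. Such an error is systematic and does not shrink with sample size.

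**Working it through.** **The plan's own figure.** The protocol gives no standard deviation, overdispersion or within-person correlation, so the claim for 500 people and 2.5 contacts cannot be reproduced forwards. Working backwards with a two-sided 5% level:

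- Analysable: 500 × 0.8 = 400.
- Implied SD of paired differences: 2.5 × √400 / (1.960 + 1.282) = about 15.4 contacts.

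This shows only that 500 is possible. The point does not rest on it; 2.5 contacts serves below as a yardstick.

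**Inputs for the illustration**

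| Input | Value | Source |
|---|---|---|
| Surveys | 5, hence 4 rounds of possible loss | Protocol, Enrolment procedure |
| Average loss | 20% | Protocol, Sample size |
| Starting share of lower socio-economic half, s | 0.50 | By definition of a half |
| Loss in lower / higher half | 30% / 10% | Assumed; averages 20% |
| Mix among replacements | 50:50 | Assumed; matching on age and sex is silent on it |
| Difference between halves | 3 contacts a day | Assumed |

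**Formulas for one round**

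- Replaced: s′ = 0.7s + 0.5 × [0.3s + 0.1(1 − s)]
- Not replaced: s′ = 0.7s / [0.7s + 0.9(1 − s)]
- Shift in the crude wave mean = 3 × (0.50 − s′). Its sign depends on which half has more contacts.

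**20% read as the total loss (one round)**

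- Replaced: s′ = 0.35 + 0.5 × 0.20 = 0.45. Shift = 3 × 0.05 = 0.15 contacts, or 6% of 2.5.
- Not replaced: s′ = 0.35 / 0.80 = 0.4375. Shift = 3 × 0.0625 = 0.19 contacts, or 7.5% of 2.5.

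**The same loss in each of four rounds**

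- Replaced: s = 0.450, 0.410, 0.378, 0.352. Shift = 3 × 0.148 = 0.44 contacts, or 18% of 2.5.
- Not replaced: s = 0.7⁴ / (0.7⁴ + 0.9⁴) = 0.2401 / 0.8962 = 0.268. Shift = 3 × 0.232 = 0.70 contacts, or 28% of 2.5. Only 0.5 × 0.8962 = 45% of the starting sample would remain.

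**Milder split, 25% / 15%, four rounds.** Shares are 0.426 (replaced) and 0.377 (not replaced), so the shifts are 0.22 and 0.37 contacts.

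**Wider ranges, still assumed.** For replaced members, bias = share replaced × shift in mix between leavers and replacements × contact difference.

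- 20% replaced, mix shift 0.1 to 0.5, difference 2 to 4: 0.04 to 0.40 contacts.
- 40% replaced, same ranges: 0.08 to 0.80 contacts.
- 20% silently missing who differ from responders by 1 to 5 contacts: 0.2 to 1.0 contacts.

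If leaving and replacement do not change the mix, every composition term is 0. All the figures above are smaller than 2.5 contacts.

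**The case against.** The strongest reply is that drift is a possibility and not a property of the plan. It needs leavers to differ from replacements, or from those who remain, on region or socio-economic status within age and sex. It distorts a comparison only if those factors also relate to contacts. The protocol gives no evidence on either. This stands: a reader might infer that the waves will drift and that their comparison is biased, and the document does not support that.

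The study is also a cohort, sized on pairs of observations and analysed with multilevel models. A participant random effect is stated for the models of exposure and contacts. Part of the contrast over time is therefore within person and less affected by who joins or leaves. This stands in part: a random effect does not return wave summaries, descriptive tables or matrices to the population margins.

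Weighting and full covariate lists are commonly left to a statistical analysis plan, which is not at hand, and income and employment status are collected and could support adjustment. This too stands, so the lack of a weighting scheme is not counted as an error. The replacement rule is different. It is fixed in the protocol, and no later analysis changes whom the company recruits.

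Two further readings go too far. One is that representativeness can hold at most for the first wave; the sentence is not limited to baseline and may be meant for every wave. In that case it sits awkwardly with a rule that matches on two variables, and the two sentences need reconciling. The other is that silent non-responders are lost for good. Only declared withdrawals are replaced, each survey completed earns an incentive, and a member who misses one wave may answer the next.

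**Conclusion.** The concern holds in a limited form. The protocol sets a four-variable standard for the sample and a replacement rule that preserves two of them, for declared withdrawals only. Composition by region and socio-economic status may therefore drift, and crude wave summaries and contact matrices would carry that drift more than the within-person contrasts would.

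A plausible size, if the 20% loss is a single total, is about 0.15 to 0.19 contacts. The 0.44 to 0.70 range needs that loss, at 30% and 10%, to recur in all four rounds, and is better read as a steep scenario. Both rest on an assumed 3-contact difference and an assumed split of the loss; with no change in mix the bias is zero. Nothing here alters the sample size or the power statement. The change is worth making because it is cheap and the possible error is systematic.

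**What to change.** 1. Amend the replacement sentence in Enrolment procedure so that replacements are matched on age, sex, geographical location and socio-economic status. The company already uses these four variables for the sample. State also that the representativeness standard applies at every wave, if that is the intention.
2. Weight each wave's population means and contact matrices to the national margins of the same four variables, for example by raking. This extends to silent non-response, which matching cannot reach, though only as far as those variables explain it. If an analysis plan already provides for this, a cross-reference is enough.

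The cost is a clause in the agreement with the panel company and a weighting step before each release. Replacement may be slightly slower, and the weights cost a little precision.

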## **Measurements**

Panel members will answer questions regarding symptoms and impact of interventions (such as school or work closures) in the seven days preceding each survey, while answering questions about their social contacts for the day preceding the survey. Surveys will be conducted using an online webform, supplied by the market research company. Data will be stored on their secure encrypted servers.

## **Survey**

During the first survey a respondent completes, we will ask certain household level characteristics including age, sex, household make-up, employment status, and income.

For every survey a respondent completes, we will ask about recent symptoms, Covid-19 tests, contact with known Covid-19 cases, and exposure and impact of different interventions, for each household member.

Impact of different social distancing interventions include:

- 1) whether household members have been asked to quarantine, isolate, work from home, or limit time spent at university (where applicable)
- 2) whether household members have had their workplace/university/school/nursery/pre-school close for at least one day in the preceding week, and
- 3) whether household members have been in quarantine, have been in isolation, have been working from home or unable to go into work/university/school/pre-school/nursery (where applicable).

We will also ask whether the respondent has been to certain events with large groups of people (such as a football match or a restaurant), whether they have taken any preventive measures (face-mask, handwashing, hand sanitizers), or whether they have used public transport.

We will also assess their attitudes and risk perceptions towards Covid-19 over time.

Finally, we will ask participants to complete a social contact survey, where we ask about all individuals contacted in the preceding day. For each contact, we will ask about their (estimated) age, sex, relationship to the respondent, general contact frequency, whether contact was physical or not, and how much time they spent with this contact.

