### Statistical analysis

We will use multilevel count models such as negative binomial regression techniques to assess the age-specific number of daily contacts, and control for confounding factors such as sex and household size. We will perform a stratified analysis by contact type (all contacts, only physical contacts, only nonphysical contacts) and setting (e.g. household, workplace, school, social settings).

The effect of any social distancing control on the average number of contacts per day will be estimated accounting for age in the multi-level model. Further to this, the individual social distancing measures will be evaluated separately. Effect modification by age and sex will be explored as appropriate.

In order to develop social contact matrices that can be used to parametrize epidemiological transmission models. We will estimate age-specific transmission parameters by correcting the age-specific daily frequency of social contacts between different age groups for the reciprocity of contacts, adjusting for the population age distribution. These estimates will be used in ongoing and future response work conducted by LSHTM and partners to help inform public policy.

We will conduct descriptive analyses of household and individual level exposures to social distancing interventions, and uptake of individual preventive measures. Frequencies will be presented in tables and exploratory analysis of the association of these measures on the number of contacts will be performed in the multilevel count models with a random effect for

participants. Attitudes and risk perceptions relating to the Covid-19 epidemic will be assessed over time visually and using descriptive statistics.

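### The closure item does not separate Covid-19 closures from scheduled ones, so closure exposure may be misclassified if a holiday falls in the ten weeks

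*Protocol*

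**What the plan says.** In the protocol's Survey section, under the lead-in "Impact of different social distancing interventions include", the second of three listed items is "whether household members have had their workplace/university/school/nursery/pre-school close for at least one day in the preceding week". The Measurements section describes the same content as "impact of interventions (such as school or work closures) in the seven days preceding each survey", while respondents report contacts by "answering questions about their social contacts for the day preceding the survey".

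The neighbouring items do not supply a reason for closure. The first item concerns requests made to household members (to quarantine, isolate, work from home or spend less time at university) and does not cover the closing of a school, nursery or workplace. The third item includes whether members "have been working from home or unable to go into work/university/school/pre-school/nursery (where applicable", again without a reason.

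In the Statistical analysis section, the effect of any social distancing control is estimated in the multilevel count model allowing for age. It continues: "Further to this, the individual social distancing measures will be evaluated separately". Sex and household size are given as examples of confounders. No term for holiday, weekday or calendar time is named. The Enrolment procedure section sets five two-weekly surveys over ten weeks in three countries, with no start date and no school calendar.

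**The concern.** Read literally, the item is met by one closed day in the week, whether the site shut because of Covid-19 or for a term holiday, public holiday or staff training day. The resulting variable is then treated as exposure to a social distancing intervention.

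Two results could be affected. One is the descriptive frequency of closure as an intervention, which would include days on which no such measure was in force. The other is the closure effect evaluated separately under objective 3, which would mix the change in contacts under epidemic closure with the change during a holiday. A wave or country term would not repair this, because it does not relabel a household whose exposure is wrongly coded. The protocol promises findings within days of each wave to guide decisions on interventions, which leaves little time to discover the problem afterwards.

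**Working it through.** **Plan's own figure.** The protocol gives no figure on this point. Its only computed figure is the detectable difference of 2.5 contacts in the Sample size section, on which this point does not depend. That figure cannot be reproduced because no standard deviation is stated. With 500 × 0.80 = 400 pairs and two-sided 5%, it implies a standard deviation of paired differences of 2.5 × √400 / (1.960 + 1.282) = 15.4.

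**Step 1: does any listed item carry the reason?** The closure item fixes duration (one day or more) and window (the preceding week). The first item is attributed to a request but covers other measures. The third records absence or home working without a cause. No described item separates an epidemic closure from a scheduled one.

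**Step 2: would a holiday meet a survey window?** Assume a holiday placed at random inside 70 days, and each survey at the end of a 14-day block looking back 7 days, so that 5 × 7 = 35 of 70 days are covered.

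- 1-day holiday: 35/70 = 0.50 chance of falling in a window.
- 7-day holiday: 64 possible start days, of which 5 lie wholly in a gap; 59/64 = 0.92.
- 14-day holiday: 1.00, touching 1.4 of the 5 waves on average.

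This shows only that a holiday of a week or more, if one occurs, would rarely be missed. It does not show that one occurs.

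**Step 3: what could it do to the results? (illustration; every input is assumed)** Let h be the share of recorded closures that are holidays, and let both kinds be compared with the same open reference group. Then

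apparent ratio = (1 − h) × ratio for epidemic closure + h × ratio for holiday.

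With an epidemic-closure ratio of 0.60:

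| Holiday ratio | h = 0.2 | h = 0.4 |
|---|---|---|
| 0.40 | 0.56 | 0.52 |
| 0.60 | 0.60 | 0.60 |
| 0.80 | 0.64 | 0.68 |
| 1.00 | 0.68 | 0.76 |

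For example, 0.6 × 0.60 + 0.4 × 0.80 = 0.68. The bias is nil when the two ratios agree, goes towards no effect when holidays reduce contacts less, and away from it when they reduce contacts more.

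On the difference scale, with assumed changes of −6 contacts for epidemic closure and −1 for holiday, a 25% holiday share gives 0.75 × (−6) + 0.25 × (−1) = −4.75 (21% smaller). A 50% share gives −3.5 (42% smaller).

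The recorded frequency of closure would exceed the true frequency of epidemic closure by a factor of 1/(1 − h): 1.25 at h = 0.2 and 1.67 at h = 0.4. This holds even where the contact effect is unbiased.

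**The case against.** The strongest reply is that the protocol never says closures count regardless of cause. The lead-in and the Measurements section both frame the item as the impact of interventions, and the list names topics rather than questionnaire wording. The questionnaire is not shown and may already ask the reason. This stands. A reader might infer that any closed day is deliberately counted, but that would be reading silence as a rule. What remains is that the described exposure has no reason attached, and a heading that respondents may not see does not define what they report.

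Second, no dates or calendars are given, so holidays in the period are an assumption. This also stands, and the point is conditional on it.

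Third, the confounder list is open-ended, and a holiday term could be built from survey date and region in an analysis plan that is not at hand. This stands in part. A calendar can mark school holidays, but it cannot tell which workplace or nursery closures were due to the epidemic. That information has to be asked for when the survey is run.

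Fourth, the section's last paragraph calls the association of exposures with contact numbers exploratory. This lowers the stakes, but objective 3 and the sentence on evaluating individual measures carry no such label.

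A further tempting inference is that the transmission models take the closure effect as the effect of the policy. The protocol does not support it: the model inputs it describes are contact frequencies by age, corrected for reciprocity and population structure. These do not depend on how closure is coded.

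**Conclusion.** The point holds in a limited form. As described, the closure item does not distinguish closures made because of Covid-19 from scheduled ones, and no holiday or calendar term is named. If a holiday falls in the ten weeks, and if the live question is no more specific than the protocol's description, exposure may be misclassified, the reported frequency of closure as an intervention may be inflated, and the closure effect may be biased.

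It would go too far to conclude that the closure effect is biased. The share of holiday closures and the difference between holiday and epidemic contacts are both unknown. The direction is open as well, since a respondent whose school holiday falls inside an epidemic closure might answer either way. The numerical examples show how the error would work and do not estimate it. This is an inexpensive improvement to make before data collection, not a demonstrated error in the results.

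**What to change.** - Record the reason in the closure item: closed because of Covid-19; closed for a scheduled holiday or other reason; open. Allow both closure answers when an epidemic closure runs into a holiday.
- In the Statistical analysis section, count only Covid-19 closure as the intervention.
- Enter scheduled holiday on the diary day as a separate covariate, from the respondent's answer checked against a national or regional school calendar.
- If the questionnaire already asks the reason, state this in the Survey section; the question then needs no change.

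The cost is a slightly longer question, a holiday calendar for each country, and some error in the reported reason, which the calendar can check for schools but less well for workplaces and nurseries. The change is cheapest before the translation and back-translation described under Regulatory details. The reason cannot be fully recovered once the surveys have been completed.

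### Any home-working in the past week counts as intervention impact, and no named item records prior home-working, so its tabulated frequency is overstated by the habitual share

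*Protocol*

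**What the plan says.** The Survey section of the protocol introduces a three-item list with "Impact of different social distancing interventions include". Item 1 is "whether household members have been asked to quarantine, isolate, work from home, or limit time spent at university (where applicable"). Item 2 covers closure of a workplace or place of education. Item 3 includes whether members "have been working from home or unable to go into work/university/school/pre-school/nursery (where applicable"). It sets no condition that the home-working began, or increased, because of a measure.

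For the first survey, the same section says "we will ask certain household level characteristics including age, sex, household make-up, employment status, and income". Usual place of work is not among the items named. The Measurements section limits the look-back: respondents report "impact of interventions (such as school or work closures) in the seven days preceding each survey". No named question about work reaches back before the epidemic.

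The Statistical analysis section uses the item in two ways. First, "We will conduct descriptive analyses of household and individual level exposures to social distancing interventions", with frequencies shown in tables. Second, "exploratory analysis of the association of these measures on the number of contacts will be performed in the multilevel count models"; a participant-level random effect is included. It also plans to evaluate each social distancing measure on its own.

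**The concern.** Item 3 as described records where someone worked in the past week. It does not record whether an intervention changed that. A person who worked at home before the epidemic can answer yes at every wave and be tabulated as affected, although nothing has changed for them.

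Items 1 and 2 do not separate this group. A habitual home-worker may also have been asked to work from home, and others may have switched without being asked. A closed workplace says nothing about where the person worked before. Repeated waves help only in part, because someone at home in every wave may be habitual or may have switched before their first survey. Members brought in as replacements may have few earlier waves or none.

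Two outputs are at stake: the reported frequency of home-working as an effect of control measures, and the separate evaluation of home-working against contact numbers. The Dissemination section plans to release findings within days of each wave to guide the scaling of interventions, so a mislabelled frequency would be used quickly. If usual place of work is not collected, it cannot be reconstructed at analysis.

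**Working it through.** The protocol gives no figure for home-working, so there is none to reproduce. Its one calculated figure, the detectable difference of 2.5 contacts, does not bear on this point.

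**Inputs.** Both are assumptions, shown as a range.
- h: share of working household members who already worked at home before the epidemic (3%, 5%, 10%, 20%).
- n: share of the remaining workers who have newly switched (10%, 50%).
- Habitual home-workers are taken to answer yes at every wave, and h is taken as stable across waves.

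**Frequency.**
- Recorded share = h + (1 − h)n
- Newly at home = (1 − h)n
- Excess = recorded − new = h, whatever n is
- Habitual share of those recorded = h / [h + (1 − h)n]

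For h = 10% and n = 10%: recorded = 0.10 + 0.90 × 0.10 = 0.19; new = 0.09; habitual share = 0.10/0.19 = 53%.
For h = 10% and n = 50%: recorded = 0.10 + 0.90 × 0.50 = 0.55; new = 0.45; habitual share = 0.10/0.55 = 18%.

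| h | n | Recorded | New | Excess (points) | Recorded / new |
|---|---|---|---|---|---|
| 3% | 10% | 12.7% | 9.7% | 3 | 1.3 |
| 3% | 50% | 51.5% | 48.5% | 3 | 1.1 |
| 5% | 10% | 14.5% | 9.5% | 5 | 1.5 |
| 5% | 50% | 52.5% | 47.5% | 5 | 1.1 |
| 10% | 10% | 19% | 9% | 10 | 2.1 |
| 10% | 50% | 55% | 45% | 10 | 1.2 |
| 20% | 10% | 28% | 8% | 20 | 3.5 |
| 20% | 50% | 60% | 40% | 20 | 1.5 |

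**Trend over waves.** With h = 10% and uptake rising from 10% to 50%, the recorded rise is 55 − 19 = 36 points and the true rise is 45 − 9 = 36 points. The absolute change is right. The ratio is not: 55/19 = 2.9-fold recorded against 45/9 = 5-fold.

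**Association with contacts.** Take illustrative means of 10 contacts for people still going out to work and 5 for those newly at home, so the true effect is −5. Let h = 5% and n = 5%. Newly at home = 0.95 × 0.05 = 0.0475; recorded as exposed = 0.05 + 0.0475 = 0.0975.

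Cross-sectional contrast = (0.05 × c + 0.0475 × 5)/0.0975 − 10, where c is the mean contacts of habitual home-workers:
- c = 3: −6.0
- c = 5: −5.0
- c = 7: −4.0
- c = 10: −2.4

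The bias can go either way and vanishes when habitual and new home-workers have the same contacts.

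Mean change since before switching, averaged over everyone recorded as exposed: (0.05 × 0 + 0.0475 × (−5))/0.0975 = −2.4. The effect is diluted to about half.

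**Frequency times effect.** Recorded: 0.0975 × (−2.44) = −0.238. True: 0.0475 × (−5) = −0.238. When the effect is the diluted within-person change, the product is unchanged.

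**The case against.** The case against has several parts.

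- **The protocol summarises a questionnaire that is not shown.** The list of first-survey characteristics is open-ended, and the impact items are topics, not question wording. The questionnaire might ask about usual workplace or tie the item to Covid-19 measures. This stands as a limit: the finding is that no such item is named, not that none exists.
- **The coding of exposure may be left to the analysis plan.** The protocol does not say how items 1 to 3 combine, and item 1 or 2 could support a stricter definition. That is a partial check only. No coding rule can identify prior home-workers from items that do not record prior home-working.
- **The affected analyses are secondary.** The protocol calls them descriptive and exploratory, and the contact matrices do not depend on this item. Current home-working is also a legitimate descriptor of present behaviour. This limits the weight of the point; it does not make the item a measure of intervention impact.
- **The size rests on assumed shares.** This is true. The 3.5-fold figure comes from the extreme corner of the range.

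A reader might also infer two stronger claims. One is that the total effect on contacts, frequency times effect, is inflated in step with the frequency. That holds only if the estimated effect keeps its true value despite the mixed group. If nothing changed for habitual home-workers, their inclusion dilutes the mean change by the same factor and the product is unchanged. The other is that early waves are the worst affected. The excess in percentage points is the same at every wave. Only the relative excess is larger when uptake is low, and the protocol does not date the first survey against any control measure, so uptake could already be high by then.

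**Conclusion.** The concern holds for the frequency. As the Survey section describes it, the tabulated share with home-working as an intervention impact exceeds the share newly at home by h percentage points at every wave. Under the assumed h = 10%, that means 19% against 9% at 10% uptake and 55% against 45% at 50% uptake. Across h from 3% to 20%, the relative overstatement runs from 1.3-fold to 3.5-fold at 10% uptake and from 1.1-fold to 1.5-fold at 50%.

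For contacts, the association of home-working with contact numbers may be biased in either direction, and the mean within-person change among those recorded as exposed is diluted. The planned participant random effect does not settle this, because a random-intercept model also draws on differences between people. A contrast restricted to people whose recorded status changes between waves would leave out constant home-workers, but also anyone who switched before their first survey.

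The conclusion assumes that the questionnaire follows the protocol's description and that habitual home-workers answer item 3 literally. It is a worthwhile, inexpensive improvement to data collection and does not undermine the study's main outputs.

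**What to change.** In the first survey each respondent completes, replacement members included, ask for the usual place of work before the epidemic of each working household member: at home, partly at home, or outside the home. If the questionnaire already asks this, the protocol need only name the item and say how it is used.

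Then report and model new or increased home-working separately from habitual home-working. Keep habitual home-workers as their own category in the tables and models, so that they are neither counted as affected nor lost from a sample meant to be nationally representative. For those who worked partly at home, the repeated item should ask whether home-working was more than usual; otherwise show them as a separate group.

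The cost is one extra question per working household member, asked once, a small wording change to the repeated item if increases are to be captured, and a recode. The downside is a slightly longer first survey and a smaller reported exposed group.
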